**Fig 1 pone.0314023.g001:**
[figure not shown]
SPIRIT schedule. The schedule highlight the timeline for patient enrollment, plans for assessment of outcomes measures during the study period. Abbreviation: t_1_ = baseline at inclusion, t_2_ = at hospital discharge, t_3_ = approximately 7 days after hospital discharge t_4_ = 30 days after hospital discharge, t_5_ = 3 months after hospital discharge, t_6_ = 6 months after hospital discharge. Abbreviations: ATC = Anatomical Therapeutic Chemical Classification System, SMR = Shared Medication Record, PIMs = potentially inappropriate medications. VAS = Visual Analogue Scale, QoL = Quality of life, MTBQ = Multi-morbidity Treatment Burden Questionnaire, Med.Coor = Medication Coordinator.

#### 2.1.1. Recruitment of patients

Patients will be recruited from the Endocrinology and Nephrology Unit at the Hospital Sønderjylland. The ward treats renal disease, diabetes, hormone disorders, patients with diabetic ulcers, and internal medicine patients. The ward comprises 16 beds distributed by rooms for two or four patients. Recruitment will commence in *medio* May 2024 and be completed by *ultimo* May 2025. We expect to include four patients weekly.

The inclusion criteria comprise all hospitalized patients 18 years or above, and are prescribed at least five medications specified in the Electronic Patient Journal (EPJ).

Patients are not eligible for inclusion if they are unable to communicate in Danish, are cognitively impaired, e.g. suffering from dementia or Alzheimer’s, or cannot cooperate due to, e.g. hallucination or aggressive behavior.

The Medication Coordinator will screen patients for eligibility and include relevant patients in the study. After the initial screening, the ward nurses are consulted regarding patient capability to contribute to a conversation about medication based on the patients habitual condition. The Medication Coordinator performs this task so the everyday workload of the ward staff is not increased or disturbed.

### 2.2. Framework for complex interventions

The MRC framework for complex intervention describes four phases: 1. Develop or Identify intervention, 2. Feasibility, 3. Evaluation, and 4. Implementation [5]. It is important to reveal what works for whom (patients), how it works (components), and under which circumstances (settings) the complex intervention is most effective [46,47]. We have developed a program theory to visualize the different components of the complex intervention (Fig 2) [5,47,48].

**Fig 2 pone.0314023.g002:**
[figure not shown]
Program theory for the study design. The program theory describes the complex intervention with inputs, activities, outputs, outcomes, and impacts. PIMs = potentially inappropriate medication.

The intervention in this study is dynamic and thus complex due to many different components, and the effect might rely on the patient’s subjective perceptions.

#### 2.2.1. The intervention group

The complex intervention was inspired by Ravn-Nielsen et al. [49] and included some adjustments. The Medication Coordinator facilitates the medication reviews in close collaboration with the patients by applying concepts of motivational interview in combination with *My Medication Plan* [50,51] [Unpublished study conducted by [name], [name], and [name]. The development of *My Medication Plan* involving patient and patient representatives as co-designers, for submission]. Furthermore, the Medication Coordinator facilitates the flow of information about medication treatment in the transition of care between healthcare sectors (Fig 3).

**Fig 3 pone.0314023.g003:**
[figure not shown]
Flow of the patient in the intervention group (I) and control group (C). Primary and secondary outcome measures are collected at inclusion, discharge, and 30 days after discharge for the evaluation of readmission and six months after for the remaining outcome measures. The dashed line represents the transition of care. Medication Risk Score = MERIS.

Based on the inclusion criteria, the patient’s contribution to the intervention and the intervention itself, the patient can withdraw his/her consent or die, otherwise there will be no criteria for the patient not being able to continue in the study after allocation.

#### 2.2.2. The control group

The patients in the control group receive usual treatment from a team consisting of hospital physicians, nurses, nurse assistants, and if required, occupational therapists, physiotherapists, and clinical dieticians. Medication reconciliation might be a part of the patients’ usual care performed by a pharmaconomist performed at the emergency department prior to allocation to another ward or a hospital physician at the ward. Hospital physicians and/or nurses might counsel patients about medication treatment during hospitalization (Fig 3).

#### 2.2.3 Medication coordinator

The Medication Coordinator’s tasks are as follows:

To empower the patients to gain control of their medication treatment [52].To collaborate with the patients through established confidence.To coordinate the communication of medication recommendations, medication changes, and implementations of the medication review made during hospitalization to the patients.To assist the patient in noting medication changes made during hospitalization and follow-up appointments across sectors in *My Medication Plan*, if desired by the patients.To contact the patients for follow-up about health status and any drug-related questions 7 days after hospital discharge by telephone.

#### 2.2.4. Medication review

The medication reviews are conducted to optimize the patients’ medication treatment. The process of optimization is through the identification of any PIMs that may be discontinued and to identify if the patients experience any drug-related problems that need to be considered. Hence, the medication review is expected to increase the quality of the patients’ medication treatment.

The definition of prescribing quality indicator used is by Lawrence and Olesen [53]: “*a measurable element of prescribing performance for which there is evidence or consensus that it can be used to assess quality*, *and hence in changing the quality of care provided* [53]”. Inspired by Wallerstedt et al [34] the measureable element of prescribing performance used to assess the quality of the patients’ medication treatment is the number of PIMs. The patients’ medications are registered according to the Anatomical Therapeutic Chemical (ATC) Classification System at level 5 [54]. The medication list is assessed for PIMs by applying: two national screening tools *(Discontinuation List 2024/2025* [35] and *the Seven High-risk Situation Medications* [36], and two international screening tools (STOPP [55] and MERIS [31,37].

The medication reviews are conducted as published by Graabæk et al. [56] but with an addition of a sixth, seventh and eight step to the existing five steps.

The patients are presented with the changes made to the medication treatment in the sixth step. The patients are encouraged to write down any important information in *My Medication Plan*. The suggested medication amendments are not implemented prior to hospital discharge, because these changes may require that the patient has been stabilized. Step 7 includes specific instructions about medication amendments in the electronic discharge summary forwarded to the GP.

As the eight step is a follow-up phone call to the patient approximately seven days after discharge. The follow-up conversations is based on the medication review carried out during hospitalization.

The concepts of motivational interviewing are applied during the medication review to focus on the patients’ needs and wishes [50,51,57,58].

#### 2.2.5. My medication plan

*My Medication Plan* is a non-electronic patient booklet consisting of a print of the SMR and specific documents sharing important medication-related information. *My Medication Plan* was developed to empower the patients and as a contribution to the information flow in the transition of care. *My Medication Plan* is available upon request albeit in Danish.

### 2.3. Data collection

Demographic variables, primary outcome and secondary outcomes will be collected at marked points (Fig 1). Some data will be collected through EPJ, an electronic healthcare system, utilized by the Region of Southern Denmark.

#### 2.3.1. Demographic variables

Demographic variables collected at baseline will include the patient’s age, sex, reason for hospital admission, and number of medications.

#### 2.3.2. Primary outcome

The primary outcome is the proportion of PIMs after hospital discharge. The PIMs are defined by four different screening tools, hence if at least one tool indicates that a medication as a PIM, we will define the medication as a PIM [31,35,36,59].

#### 2.3.3. Secondary outcome

The secondary outcomes are patient-reported outcomes about quality of life and treatment burden after 3 months, but also patient’s readmissions, and contact to the ward after 30 days. The patient’s MERIS score is calculated to estimate if a medication review could change the MERIS score and reduce the probability of experiencing a drug-related problem.

*2*.*3*.*3*.*1*. *Patient-reported outcome*. To measure patient-reported outcomes regarding the quality of life and treatment burden, the *EuroQol-5* Domain (EQ-5D) and Multi-morbidity Treatment Burden Questionnaire (MTBQ) are used [55,57]. The questionnaires are combined with a Visual Analogue Scale (VAS) regarding quality of life and treatment burden as validation. VAS assessment of subjective phenomena will be converted to numerical data [60].

The patients will fill out EQ-5D, EQ-VAS, MTBQ, and the two VAS’s at inclusion and hospital discharge. The same questionnaires are answered three months after hospital discharge, either by e-mail or telephone, conducted by the first author.

EQ-5D contains five questions regarding five domains: mobility, self-care, usual activities, pain/discomfort, and anxiety/depression, each with five answer categories: no problems, slight problems, moderate problems, severe problems, and extreme problems. Permission to use the Danish EQ-5D version has been granted by EuroQol [61].

The EQ-VAS is a vertical VAS in which patients report their perceived quality of life from 0–100 [61]. The endpoints are labelled with “*The worst health you can imagine*” (0) and “*The best health you can imagine*” (100) [61]. These measurements are used to quantify a health outcome that reflects the patient’s perception.

An additional VAS regarding quality of life is added to validate if the VAS can be applied instead of a questionnaire. The questionnaire used for the validation is the ED-Q5.

The VAS is vertical and ranges from zero (lowest quality of life) to 100 (highest quality of life) by numbers. The question asked is: “How is you quality of life today?” The endpoints are labelled with “*The worst quality of life you can imagine*” (0) and “*The highest quality of life you can imagine*” (100).

The MTBQ is a validated tool to assess patients’ perceived treatment burden [62]. Treatment burden describes patients’ perceptions of the effort required to look after their health and its effect on everyday life [63]. A Danish version of the MTBQ has been validated [64] and will be used with permission.

The MTBQ is a ten-item questionnaire with good content validity, high internal reliability, and good construct validity [62]. The questions cover medication management, self-monitoring, contact with healthcare professionals, obtaining information, implementing lifestyle changes, and relying on help [62,64]. The answers are designed with a five-point Likert scale with the possibilities: “*Not difficult*” (0), “*A little difficult*” (1), “*Quite difficult*” (2), “*Very difficult*” (3), “*Extremely difficult*” (4), and “*Does not apply*” (0) [62]. The MTBQ scores are categorized into no burden (score 0), low burden (score < 10), medium burden (score 10–22), and high burden (score ≥ 22) [62,64].

An additional VAS regarding treatment burden will be added to validate if the VAS can be applied instead of a questionnaire. The questionnaire used for the validation is the MBTQ.

The VAS is vertical and ranges from zero (no burden at all) to 100 (the highest burden imaginable) by numbers. The questions asked is: “How much of a burden is it for you to manage your illness today?” The endpoints are labelled with “*The highest burden it is for you to manage your illness*” (0) and “*The least burden it is for you to manage your illness*” (100).

*2*.*3*.*3*.*2*. *Hospital readmission*. Patient readmissions are assessed via EPJ 30 days after hospital discharge. As the data regarding readmissions will only be collected through EPJ—readmission data can only be collected from the Region of Southern Denmark [no other regions in Denmark].

*2*.*3*.*3*.*3*. *Contact to the ward*. Patient contact with the ward will be evaluated based on justification for the contact, e.g. medication-related questions. Data will be collected via EPJ 30 days after hospital discharge.

*2*.*3*.*3*.*4*. *Patients’ Medication Risk Score*. The patient’s MERIS will be calculated at inclusion and hospital discharge using the Software Robot Sirenia Manatee [31,37]. The MERIS algorithm provides a score reflecting the risk of probability for the patients experiencing a serious drug-related problem [37]. The MERIS score is calculated for all patients included in the study to assess which patients would benefit most from a medication review. The calculation is based on the patients’ most recently measured, estimated glomerular filtration rate value, the number of medications, and the risk of a drug to cause harm or interactions. The medications with risk for harm or interactions are described in the literature [29,65,66]. Data will be collected via EPJ.

*2*.*3*.*3*.*5*. *Follow-up after discharge*. In the follow-up conversation between the patient and the Medication Coordinator, data about which medication(s) and which topic regarding the medications(s) are collected. Furthermore, data about the usage of *My Medication Plan* are collected to be used in the reporting of the feasibility of the complex intervention.

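### At three months, the patient-reported endpoint may be answered by e-mail or by telephone with the person who delivers the intervention, so a telephone VAS becomes a spoken number and arm-level bias cannot be excluded

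*Protocol article*

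**What the plan says.** Section 2.3.3 of the protocol article fixes the time point: "The secondary outcomes are patient-reported outcomes about quality of life and treatment burden after 3 months".

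Section 2.3.3.1 then describes two ways of collecting the answers. In hospital: "The patients will fill out EQ-5D, EQ-VAS, MTBQ, and the two VAS’s at inclusion and hospital discharge". At the endpoint: "The same questionnaires are answered three months after hospital discharge, either by e-mail or telephone, conducted by the first author".

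The scales are defined visually. "The EQ-VAS is a vertical VAS in which patients report their perceived quality of life from 0–100", with labelled ends. For the added quality-of-life scale: "The VAS is vertical and ranges from zero (lowest quality of life) to 100 (highest quality of life) by numbers". The treatment-burden scale has the same vertical, numbered form. Both added scales have a validation purpose; for burden it reads: "An additional VAS regarding treatment burden will be added to validate if the VAS can be applied instead of a questionnaire".

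Section 2.6.2 analyses these outcomes over their time points with the tests of section 2.6.1: a global test of the intervention, followed by tests of the treatment effect at each time point. Section 2.1 gives screening, enrolment, randomisation and assessments to one person. The Discussion lists as a limitation that the first author performs the intervention.

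**The concern.** The mode of answering changes between discharge and the named endpoint, and it is mixed at the endpoint. This raises three issues.

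- **The scale.** A vertical line with labelled ends cannot be shown by telephone, so the patient gives a number in reply to what the caller says. This matters most for the burden scale, whose description and end labels in section 2.3.3.1 run in opposite directions. That is a separate defect, but a patient on the telephone sees no labels and depends on the caller for the direction.
- **The listener.** A telephone answer goes to the first author. For an intervention patient, that is the person who reviewed their medication and called about a week after discharge. For a control patient it is not. The Discussion itself names social-desirability bias in the questionnaires. Blinding the data analyst (section 2.6) does not protect the answer at the moment it is given.
- **The validation.** The aim is to learn whether a VAS could replace a questionnaire. A spoken number answers that for a different form of the scale.

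At stake are the three-month comparison of quality of life and burden, and the use of three-month records in the validation. The primary outcome is not involved.

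**Working it through.** The article gives no figure on this point to reproduce. The check asks when a mode effect reaches the arm contrast, and how large it could be.

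**Inputs.** From the article: 70 patients per arm (section 2.5) and two-sided 5% significance (section 2.6). Assumed, because the article gives neither: a telephone-versus-self-completion effect *m* of 0.1 to 0.3 SD, and telephone shares *p* of 50/50, 60/40 or 70/30 (intervention/control). Simplifications: complete follow-up, a normal approximation in place of the planned beta-binomial model, and a single unadjusted comparison.

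**Step 1: general form.** Bias in the three-month arm contrast = p_I × m_I − p_C × m_C. The shift in an arm's own change from discharge = p × m. The standard error is √(2/70) = 0.169 SD. For a bias *b*, the false-positive rate is 1 − Φ(1.96 − b/SE) + Φ(−1.96 − b/SE).

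**Step 2: same share and same effect in both arms.** The bias is 0 and the false-positive rate 5%, whatever *m* is. A simulation of 20,000 trials gave rejection rates of 4.6% to 5.2%. Each arm's own trend still shifts by 0.5 × 0.1 = 0.05 SD to 0.5 × 0.3 = 0.15 SD.

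**Step 3: same effect, different shares.** Bias = m × (p_I − p_C).

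| Shares | Bias, m = 0.1 to 0.3 | False-positive rate |
|---|---|---|
| 60/40 | 0.02 to 0.06 SD | 5.2% to 6.5% |
| 70/30 | 0.04 to 0.12 SD | 5.6% to 10.9% |

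The simulation at m = 0.3 gave 6.3% and 10.7%.

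**Step 4: same share, different effect.** Bias = p × (m_I − m_C). This is the route through the intervention provider. With p = 0.5 and an assumed difference of 0.1 to 0.3 SD, the bias is 0.05 to 0.15 SD and the false-positive rate about 6% to 14%. Equal telephone shares do not remove it.

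**Step 5: validation.** VAS and questionnaire are given together at each occasion, so inclusion and discharge pairs are untouched. For three-month pairs, suppose half are by telephone and the telephone shifts only the VAS. An assumed correlation of 0.70 then falls to about 0.69 for a 0.3 SD shift and 0.68 for 0.5 SD. If pairs were pooled over three complete occasions, which the article does not say, a telephone share of 30% to 70% at three months would make 30/3 = 10% to 70/3 = 23% of all pairs telephone answers.

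**The case against.** The strongest reply is that randomisation already protects the comparison that matters. The planned tests compare arms, and a mode change common to both arms drops out, as step 2 shows. No stated objective or test concerns change within an arm from discharge to three months, so a shifted trend touches no planned conclusion. This stands.

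A reader might infer that the trial uses different instruments at three months. The article does not support that: it says the questionnaires are the same. EQ-5D and MTBQ items have fixed categories that can be read aloud, and the added scales carry numbers, so a spoken number is not far from them. What changes is the mode; only the visual form of the VAS is lost.

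A reader might also infer that the arm contrast is biased because intervention patients are used to telephone contact from the day-7 call. The article describes that call but does not link it to the mode at three months. Bias remains possible and is not shown.

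Nor does the article say that VAS pairs will be pooled over occasions, or whether patients get help when they fill out the forms in hospital. A rule for choosing the mode may stand in the full protocol or analysis plan, so its absence from an article is not the finding. A second route of contact may also reduce the loss at the third questionnaire that the Discussion expects.

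What remains is what the article does state: a mixed-mode endpoint, a visual scale that one mode cannot show, and answers collected by the person who delivers the intervention.

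**Conclusion.** The point holds as a limited one. Three-month telephone answers turn a visual scale into a spoken number, given to someone who knows the patient's allocation. They should not count as validation of the visual scale; inclusion and discharge pairs can. The arm contrast is unaffected by any mode effect the arms share. It is biased only if the telephone share, or the effect of speaking to the provider, differs by arm, and the article neither shows nor excludes either.

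Under the assumed inputs the bias runs from zero to about 0.15 SD, less than one standard error (0.169 SD). The false-positive rate runs from 5% to about 14%, the upper end needing a 0.3 SD difference between arms in the telephone effect. Every mode effect and telephone share behind these figures is assumed. This concerns secondary outcomes, and the change is a cheap improvement.

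**What to change.** In section 2.3.3.1, make self-completion by e-mail, showing the same vertical scale, the first mode for every patient. Use the telephone only after a fixed number of reminders, under the same rule in both arms. Record the mode of each answer in REDCap.

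In section 2.6.2, report mode by arm and base the VAS validation on self-completed records. The three-month arm comparison should keep all answers. A comparison adjusted for mode, or restricted to self-completed answers, should be exploratory only: mode is determined after randomisation, and conditioning on it can introduce selection.

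The cost is one contact rule, one database field, a few more reminders, and fewer records in the VAS validation.

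### MERIS is scheduled at inclusion and discharge; if the suggested amendments start only after discharge, it misses most or all of the change it is meant to detect

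*Protocol article*

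**What the plan says.** **Purpose.** Section 2.3.3 lists MERIS among the secondary outcomes: "The patient’s MERIS score is calculated to estimate if a medication review could change the MERIS score", with a lower probability of a drug-related problem as the hoped-for result. Section 2.3.3.4 adds a second purpose: "The MERIS score is calculated for all patients included in the study to assess which patients would benefit most from a medication review".

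**Measurement times.** Section 2.3.3.4: "MERIS will be calculated at inclusion and hospital discharge using the Software Robot Sirenia Manatee". It names no time after discharge. The score is built from the latest eGFR, the number of medications, and the harm or interaction risk of the drugs.

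**When the review takes effect.** Section 2.2.4: "The suggested medication amendments are not implemented prior to hospital discharge". Step 7 of the review passes instructions on the amendments to the GP in the electronic discharge summary. Section 2.2.3, however, lists among the coordinator's tasks the communication of "implementations of the medication review made during hospitalization to the patients". Step six in section 2.2.4 also has patients shown changes made to their treatment.

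**Other statements on timing.** The Fig 3 caption gives 30 days for readmission and "six months after for the remaining outcome measures". Section 2.3.3 places the questionnaires elsewhere: "The secondary outcomes are patient-reported outcomes about quality of life and treatment burden after 3 months". Section 2.6.2 applies the test of the primary analysis to MERIS, and section 2.6.1 gives the time points of that analysis as baseline, discharge and six months.

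**The concern.** An outcome can show an effect only if it is measured after the effect has had a chance to occur. Here the stated purpose of MERIS (does the review change it?), its stated times (inclusion and discharge) and the stated route of the intervention (amendments made after discharge, through the GP) do not fit together. None of the three components of the score moves because of an amendment that has not yet been made.

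The risk is a misread null. A MERIS comparison showing no difference at discharge could be reported as evidence that the review does not lower medication risk, when the score was taken before the suggested amendments were due to begin. The article also gives conflicting signals on whether a later MERIS exists, so a reader cannot tell which comparison will be reported as the MERIS result.

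**Working it through.** The article states no effect size or power for MERIS, so there is no figure to reproduce. The check is a comparison of the text, followed by an illustration.

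**Step 1. Order of events, following sections 2.2.4 and 2.3.3.4**

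| Event | Time | Source |
|---|---|---|
| First MERIS | inclusion | 2.3.3.4 |
| Review, with suggested amendments | during the stay | 2.2.4 |
| Second MERIS | discharge | 2.3.3.4 |
| Amendments sent to GP | with the discharge summary | 2.2.4, step 7 |
| Amendments take effect | after discharge | 2.2.4 |
| Later MERIS | none named | 2.3.3.4 |

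At discharge the medication lists in both arms are without the suggested amendments. Shifts in eGFR and usual-care changes do affect the score, but randomisation balances them in expectation. The suggested amendments therefore add nothing to the arm difference at discharge.

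**Step 2. What could still appear at discharge.** Section 2.2.3 and step six can be read as allowing some review-driven change in hospital. A discharge score would capture that share and miss whatever is left to the GP.

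**Step 3. Is a later MERIS implied elsewhere?** Read literally, the Fig 3 caption puts every outcome other than readmission at six months, and its legend names MERIS. Section 2.6.2 points the same way by borrowing the primary test, but less firmly: the questionnaires get that test too, and their text describes no six-month measurement. Section 2.3.3.4 provides no six-month score for either.

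**Step 4. Illustration of size.** Inputs: n = 70 per arm (section 2.4, where it was derived for the PIM outcome), two-sided alpha 0.05 (critical value 1.96). Assumptions: an eventual standardised effect d when all amendments are in force; a share f in force when MERIS is taken; an effect proportional to f; no dropout.

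Power = Φ(f·d·√(n/2) − 1.96) + Φ(−f·d·√(n/2) − 1.96), with √(70/2) = 5.916.

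For d = 0.5 and f = 0.5: 0.25 × 5.916 = 1.479, and Φ(−0.481) + Φ(−3.439) ≈ 0.316. For d = 0.5 and f = 1: 0.5 × 5.916 = 2.958, and Φ(0.998) + Φ(−4.918) ≈ 0.841.

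| d (assumed) | f = 0 | 10% | 25% | 50% | 100% |
|---|---|---|---|---|---|
| 0.3 SD | 5.0% | 5.4% | 7.3% | 14.4% | 42.7% |
| 0.5 SD | 5.0% | 6.0% | 11.5% | 31.6% | 84.1% |
| 0.8 SD | 5.0% | 7.6% | 21.9% | 65.8% | 99.7% |

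The first column does not depend on d: with nothing in force, the chance of a significant result is the type I error rate, whatever the review later achieves.

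**The case against.** **The discharge effect need not be zero.** A reader might infer that MERIS is bound to show no difference. The documents do not support that without conditions. Section 2.2.4 excludes only the suggested amendments before discharge; section 2.2.3 and step six mention changes or implementation during the stay. The wording in 2.2.3 is itself ambiguous, since the reference to hospitalisation may describe the review and not date the implementation. This stands: the zero effect and the 5% apply only if section 2.2.4 governs and no review-driven change occurs in hospital.

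**It is not certain that no later MERIS is planned.** Section 2.3.3.4 does not say that its two times are the only ones. The Fig 3 caption suggests a six-month value, and Fig 1, the outcome schedule, could not be seen. This also stands in part. But if a six-month MERIS is planned, the section that defines the outcome omits it and needs correcting.

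**The second purpose is unharmed.** The inclusion score can be used to study who benefits most from a review. This stands in full, so the point does not make MERIS useless.

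**Questionnaire timing.** A reader might infer from the clash between three and six months that the questionnaire endpoint could be chosen after the data are seen. The documents do not support this. Section 2.3.3 gives three months twice, the Fig 1 caption defines a three-month visit, the discussion counts three questionnaires, and no section of the text describes one at six months. Only the Fig 3 caption is out of line, which is an editorial matter.

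**Conclusion.** The point holds with its conditions attached. On the text of sections 2.3.3, 2.3.3.4 and 2.2.4, MERIS is taken too early for the purpose of showing change: at discharge it misses most or all of the intended effect, and any in-hospital change is captured only in part. For an assumed eventual effect of 0.5 SD, power runs from 5% with none of the amendments in force to 32% with half and 84% with all. The effect sizes and shares are assumptions; the dependence on timing follows from the text.

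Separately, the MERIS times are not stated consistently across the Fig 3 caption, section 2.3.3.4 and section 2.6. This concerns one secondary outcome. It should be corrected, but it does not affect the PIM primary outcome or the use of the inclusion score for prioritisation.

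**What to change.** 1. Calculate MERIS at six months for all patients, from the medication list needed for the primary outcome and the most recent eGFR in the EPJ.
2. Name the six-month between-arm difference, adjusted for inclusion MERIS, as the MERIS effect endpoint. Report the discharge score as descriptive.
3. Keep the inclusion score for the prioritisation question.
4. If a six-month score is not feasible, drop the aim of showing a change in MERIS and keep only the prioritisation purpose.
5. State the same MERIS times in the Fig 3 caption and in sections 2.3.3, 2.3.3.4 and 2.6.2, and check Fig 1 against them.
6. Correct the Fig 3 caption to three months for the questionnaires.
7. Reconcile sections 2.2.3 and 2.2.4 on when medication changes take place.

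**Cost.** One further software-calculated score per patient and an amendment communicated to the registry, as section 2.8 provides for. Because the score uses the most recent eGFR, no new visit or blood test is needed, but some values will be old at six months. It is assumed that the software can be run on the six-month list for discharged patients; the article does not say so, and this should be confirmed first.
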